Patients will be divided into two groups based on their medical history: (i) Group A: SMuRF-less patients, (ii) Group B: Patients with SMuRFs, defined as those who fulfilled at least one of the following criteria: (i) known history of hypertension and/or antihypertensive treatment prior to AMI, (ii) self-reported use of tobacco products on a systematic basis for up to 12 months before AMI, (iii) history of diabetes mellitus type 1 or 2 and/or treatment with antidiabetic tablets or insulin before AMI or diagnosis of diabetes mellitus based on HbA1c during AMI hospitalization, (iv) known hypercholesterolemia (total cholesterol > 200 mg/dl / LDLc > 150 mg/dl) or treatment with statins or PCSK9is, before AMI. SMuRF-less patients (Group A) are defined as those suffering an AMI in the absence of these comorbidities.

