### Data collection and study procedures

After obtaining written informed consent, the following clinical characteristics will be recorded for each patient: demographics, socioeconomic parameters, complete medical history and medication, prior diagnostic and therapeutic interventions. A self-reported measurement of patients’ physical activity will be provided using the International Physical Activity Questionnaire (IPAQ), which will be completed by each patient before discharge. IPAQ is a validated questionnaire utilized to objectively measure and stratify physical activity by dividing populations into three levels: low, moderate and high physical activity [13]. Obesity will be diagnosed by categorization of body mass index (BMI; Kg/m2) measured before echocardiographic study. Recorded socioeconomic parameters will include education, marital status, employment, income, migration background and ethnicity. Moreover, the 36-item short form (SF-36) standardized questionnaire will be administered to obtain a self-reported measure of their health-related perception of quality of life before the AMI. In addition, patient laboratory data will be recorded on admission and during hospitalization. These include total blood count, standard biochemistry parameters, coagulation tests, thyroid hormone and thyroid-stimulating hormone levels, HbA1c, NTproBNP and HsTnT levels on admission, peak values of HsTnT, and NTproBNP. Moreover, levels of LP(a), apolipoproteins B and A1 (ApoB and ApoA1) interleukin-6 (IL-6) and soluble urokinase plasminogen activator receptor (suPAR) on admission will be assessed. Additionally, coronary angiographic images of every patient will be evaluated by two experienced independent interventional cardiologists blinded as to the demographic and clinical patient characteristics. Angiographic parameters such as lesion characteristics, coronary dominance and the SYNTAX score will be calculated.

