Baseline patient characteristics of each group will be examined and compared using the chi-square test for categorical variables and the 2-sided Student’s t-test for continuous variables or non-parametric tests (Wilcoxon, Mann-Whitney U etc.), when assumptions of normality are not met. Categorical variables will be represented by frequencies and percentages (%) and continuous variables will be summarized by mean ± standard deviation (SD) or median (1st -3rd quartile), as appropriate. In terms of statistical tests recruited for outcomes calculation, the two groups of patients will be compared to each other to identify clinical, laboratory and imaging biomarkers associated with a higher or lower probability of developing a SMuRF-less AMI. The chi-square test will be used to compare the prevalence of clinical parameters among patients with and without SMuRFs, and the t-test and Mann-Whitney U test will be utilized to compare the mean levels of laboratory and imaging biomarkers between the two groups. As mentioned before, univariate linear and logistic regression analyses will be applied to calculate univariate odds ratios, and then multivariate regression analyses will be performed. Finally, in order to identify the optimal combination of epidemiological, clinical, laboratory and imaging biomarkers associated with SMuRF-less AMIs, supervised machine learning algorithms will be used. The resulting clinical-laboratory prediction models will be evaluated with Receiver Operating Characteristic (ROC) curves.

A time-to-event analysis will be performed to assess whether the absence of SMuRFs is associated with better or worse clinical prognosis of patients (secondary outcome). Event rates will be compared by the long-rank test. Μultivariable Cox proportional hazard models will be utilized to adjust the results for clinically relevant and univariately significant variables. The 2-tailed p value of 0.05 will be considered the significance threshold for all statistical tests. All outcomes will be reported with 95% confidence intervals. Data management and statistical analyses will be conducted using SPSS software, version 26 (IBM SPSS Statistics) and R version 3.4.4 (R Foundation for Statistical Computing, Vienna, Austria).

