Regarding imaging biomarkers, the innovation of the study lies in the fact that it recruits conventional and novel echocardiographic parameters and analytical angiographic assessment to unravel differences among SMuRF-less patients compared to patients with SMuRFs. As novel imaging modalities have proved, plaque vulnerability and rupture electromechanical complications are not always directly associated with systematically assessed biomarkers and risk factors such as dyslipidaemia [43, 44]. Moreover, an observational study by Figtree et al. indicated differences in the prevalence of left main and left anterior descending culprit lesions in SMuRF-less patients compared to those with SMuRFs [27]. As explained by the authors, this may be partly attributed to the family history of premature CAD and is an important finding potentially leading to a more adverse AMI risk profile in SMuRF-less patients. A potential criticism that our study could deal with is that differences in imaging parameters between patients with and without SMuRFs are likely to be the consequence of AMI rather than a predictive parameter. However, the main objective of the study is to identify associations of clinical, laboratory and imaging variables with SMuRF-less status which should be tested in future larger trials for their predictive value. Thus, the elaboration of additional biomarkers, such as imaging parameters, could contribute to the characterization of the clinical profile of SMuRF-less patients hospitalized with AMI, and shed light on the etiology of this emerging clinical entity. Finally, this study aims to provide data on the prognosis of SMuRF-less AMIs and evaluate emerging evidence highlighting the worse clinical course of these patients [3, 5, 6, 45–49]. The reason behind this observation could be correlated with increased time-to-reperfusion time due to reduced suspicion of AMI in these individuals, but also with undiscovered pathogenetic mechanisms and ‘‘hidden’’ comorbidities which might increase their cardiovascular risk.

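### The covariate rule for the prognosis Cox model has no timing criterion, so post-onset severity markers and the defining SMuRFs can enter and attenuate or change the SMuRF-less contrast

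*Protocol article*

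**What the plan says.** In the protocol article, Statistical analysis, the time-to-event analysis is there "to assess whether the absence of SMuRFs is associated with better or worse clinical prognosis of patients (secondary outcome"). It has two parts. First, "Event rates will be compared by the long-rank test" (a misprint for log-rank). Second, multivariable "Cox proportional hazard models will be utilized to adjust the results for clinically relevant and univariately significant variables". The significance threshold is 0.05, two-sided, for all tests. No covariate is named and no class of variable is excluded.

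The exposure is defined under Study design and population: "SMuRF-less patients (Group A) are defined as those suffering an AMI in the absence of these comorbidities". The comorbidities meant are hypertension, tobacco use, diabetes and hypercholesterolaemia, with treatment included in the definition for all but smoking.

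The variables available to the rule are listed under Data collection and study procedures. They include "complete medical history and medication, prior diagnostic and therapeutic interventions", laboratory values such as "NTproBNP and HsTnT levels on admission, peak values of HsTnT, and NTproBNP", the SYNTAX score, and echocardiography within 24 hours of admission with LVEF, strain and myocardial work.

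**The concern.** The analysis asks how patients without SMuRFs fare compared with patients who have them. A covariate belongs in that model if it confounds the comparison, which in practice means that it was present before the infarction and does not itself define the groups. The stated rule tests for neither.

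Two kinds of variable can get in.

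- **Post-onset severity markers.** They are clinically relevant and tend to predict outcome, so they are well placed to pass. The Discussion suggests that a worse course may be related to "increased time-to-reperfusion time due to reduced suspicion of AMI in these individuals". Infarct size and ventricular function would be downstream of such a delay, and adjusting for them takes out that part of the group difference.
- **The SMuRFs themselves.** SMuRF-less status is a function of the four. Once one or more is in the model, the coefficient no longer compares SMuRF-less patients with all patients who have SMuRFs.

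At stake is the meaning of the adjusted hazard ratio. A reader could take a value near 1 as evidence of no excess risk when the model has conditioned on part of the route by which the risk arises.

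**Working it through.** The plan gives no hazard ratio, event count or power for the Cox analysis, so there is no stated figure to reproduce. Its 75 SMuRF-less patients among 500 (75 / 0.15 = 500) belong to the logistic analysis. What follows shows how the rule behaves. All effect sizes, prevalences and event rates are assumed.

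**1. Adjusting for a mediator.** If a share m of the log-HR runs through a severity marker, then approximately

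log HR(adjusted) = (1 − m) × log HR(total).

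Inputs: 15% SMuRF-less; marker shifted by −0.5 SD; log-HR −0.5 per SD of the marker; direct log-HR 0.25. The mediated part is (−0.5) × (−0.5) = 0.25, so m = 0.25 / 0.50 = 0.5. Cox models fitted to simulated cohorts gave HR 1.61 without the marker and 1.27 with it. On the log scale that is 0.476 and 0.239, so half remains, as the inputs dictate.

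**2. A second simulation with a total HR of 1.5.** Four independent SMuRFs with prevalences 45%, 45%, 20% and 42% give 0.55 × 0.55 × 0.80 × 0.58 = 14% SMuRF-less. The severity marker is shifted by 0.5 SD and follow-up is two years. Large-cohort HRs when the SMuRFs have no effect of their own:

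| Covariates beside SMuRF-less status | 0% mediated | 50% mediated | 100% mediated |
|---|---|---|---|
| Age | 1.49 | 1.49 | 1.49 |
| Age + severity marker | 1.50 | 1.24 | 1.02 |
| Age + four SMuRFs | 1.44 | 1.50 | 1.53 |

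The formula gives 1.5^0.5 = 1.22 and 1.5^0 = 1.00 for the last two cells of the severity row, in line with 1.24 and 1.02. The spread 1.44 to 1.53 in the last row is simulation error around 1.5.

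**3. Would the screen select such variables at n = 500?** In 300 simulated trials per scenario, screening at p < 0.05 picked the severity marker in 94% to 100% of runs. The median HR, age-adjusted against screened, went from 1.45 to 1.13 (half mediated) and from 1.45 to 0.96 (fully mediated). These medians carry simulation error, so the large-cohort fall from 1.49 to 1.24 is the steadier guide for half mediation. SMuRFs without an effect of their own were picked in 4% to 11% of runs. One given a log-HR of 0.4 was picked in 25%.

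**4. Adding the SMuRFs.** With all four forced in at n = 500, the standard error of the log-HR rose from 0.294 to 0.418, a ratio of 0.418 / 0.294 = 1.42. This agrees with the overlap between status and its components: R² of 0.35 to 0.49 gives a variance inflation of 1 / (1 − R²), about 1.5 to 2.0. When SMuRFs carry their own effects on the hazard (log-HRs 0.1, 0.1, 0.4 and 0), adding them moved the HR from 1.24 to 1.53 with nothing mediated. The movement follows the sign of those effects. Components associated with lower hazard would move it down.

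**5. Room for lost precision.** With 15% allocation, two-sided 0.05 and 80% power, the events needed are 7.85 / (0.15 × 0.85 × (ln HR)²): 375 for HR 1.5 and 129 for HR 2. If 15% of 500 patients had an event (75, assumed, for whichever endpoint), power would be 24% and 57%.

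**The case against.** Several points on the other side are fair.

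- **The rule has a judgement condition.** Clinical relevance is required as well as univariate significance, and a condensed article may leave the covariate list to a fuller plan. That stands as a caution: the document does not say that LVEF or any SMuRF will be entered. But relevance excludes neither kind of variable, and what is printed is a selection rule, not a silence.
- **The SMuRFs may seldom pass.** If both conditions are needed, the screening rates in step 3 make it too strong to call them likely to enter. If the wording means either condition suffices, they could enter on relevance alone.
- **The pathway is conjecture.** The Discussion offers delayed reperfusion as a possible explanation, and time to reperfusion is not listed among the recorded variables. SYNTAX score grades coronary disease complexity and is not presented as a result of delay. Hence the point is that some post-onset variables may be mediators, not that all are.
- **An unadjusted comparison is planned.** The log-rank test reports it whatever enters the Cox model. It does not handle confounding by age, sex or other prior characteristics, so it cannot stand in for a sound adjusted estimate.
- **A severity-adjusted question is legitimate.** The article asks about association and disclaims causal conclusions. Whether status adds prognostic information beyond presentation severity is worth asking, but it is a different question and should be labelled as such.

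A reader might infer that the rule removes the prognostic effect or leaves the adjusted HR uninterpretable. The documents do not support either. Removal needs the mediated part to account for the whole group difference. Adding SMuRFs alters the contrast and costs precision, but the four indicators are not exactly collinear with the exposure.

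**Conclusion.** The concern holds in a limited form. The stated rule lets post-onset severity variables and the components of the exposure into the model that is meant to estimate the prognosis of SMuRF-less patients, and nothing else in the article keeps them out. Which quantity the adjusted HR estimates would then depend on which variables happen to pass.

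Severity adjustment attenuates by the mediated share, which is unknown here. The illustrated range runs from no change to almost complete loss, with 1.61 to 1.27 at one half. Component adjustment changes the comparison, raises the standard error by about 40% if all four enter, and can shift the HR either way. These sizes rest on assumed effects, independent SMuRFs and assumed event rates. They describe the rule and do not predict this trial's result. The analysis is secondary and observational, so the point is a recommended change and does not threaten the primary comparison.

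**What to change.** Replace the univariate-significance rule with two prespecified models, for example:

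*The main Cox model contains SMuRF-less status and a short list of pre-AMI confounders chosen on subject-matter grounds: at least age and sex, with other recorded pre-AMI characteristics as the number of events allows. Hypertension, diabetes, hypercholesterolaemia, smoking and their treatments are not entered alongside SMuRF-less status. A second, explanatory model adds AMI type and post-onset severity variables (LVEF, strain, peak hs-TnT, NT-proBNP, SYNTAX score) and is reported as adjusted for possible mediators. The conclusion on prognosis rests on the main model.*

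Age and sex alone would be a thin set. The article also records socioeconomic factors, body mass index and medical history, from which the investigators can choose before seeing outcomes.

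The change is to analysis wording and needs no new data. The main model will explain less of the variation in outcome than one with severity variables. The severity-adjusted result is kept, under its proper name.

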## Discussion

‘’Beyond-SMuRF’’ is a prospective cohort trial, enrolling recently hospitalized patients with AMI and aspiring to identify clinical, laboratory and imaging biomarkers associated with SMuRF-less status. So far, suggested polygenic clinical risk-score models seem to underestimate the risk in SMuRF-less patients and are usually incapable of identifying cardiovascular risk factors on top of SMuRFs [18]. Therefore, the rationale of this study is -by comparing clinical, laboratory, echocardiographic and angiographic parameters between the SMuRF-less group and the group of patients with SMuRFs- to assess novel biomarkers as predictors of SMuRF-less AMIs and ultimately generate a risk-stratification tool for this increasingly recognized entity. To our knowledge, this is the first study to comprehensively attempt an in-depth, multiparametric evaluation of the profile of SMuRF-less population with AMI. Although several studies have reported clinical outcomes in SMuRF-less patients, there is a lack of evidence regarding clinical, laboratory and imaging findings in these patients.

Several studies have reported baseline demographic characteristics among patients with and without SMuRFs [3, 11, 18, 19]. Ηowever, no marked differences have been explored so far between the two groups in terms of basic demographic features such as age and sex. Moreover, differences in baseline clinical characteristics and comorbidities have not been thoroughly evaluated on a systematic basis, which adds to the novelty of this study. For instance, rheumatic and autoimmune diseases, as well as abdominal obesity, alcohol consumption and drug use, have been associated with increased cardiovascular risk but have never been assessed as potential absolute explainers of SMuRF-less AMIs [18, 20]. Furthermore, mental health status and psychosocial risk factors have been linked to CAD, but data regarding the association thereof with SMuRF-less status in AMI are lacking [20–24]. Additionally, the lack of physical activity, as well as specific socioeconomic parameters, have been proven drivers of CAD, but never evaluated in the context of SMuRF-less AMIs [24–26].

Moreover, the laboratory profile of SMuRF-less patients remains understudied. In general, there is an absence of available and specific blood work-up biomarkers of CAD beyond markers indicating SMuRFs. In a retrospective analysis of the SWEDEHEART registry, the authors found lower body-mass index, lower triglyceride concentrations, and higher HDL-C concentrations in the SMuRF-less group versus patients with SMuRFs, which probably suggests that these factors might not drive the atherosclerosis [27]. Only few studies have been conducted to indicate blood markers associated with AMI in these patients, but none of them showed remarkable results or studied non-conventional biomarkers [4, 27, 28]. Consistent with the hypothesis that a significant number of mechanisms underlying atherosclerosis and ACS without SMuRFs remains undiscovered, our study will be the first to elaborate metabolomic and inflammatory biomarkers, such as Lp(a), ApoB and ApoA1 interleukin-6 (IL-6) and suPAR. Although an increasing number of registries assess the impact of such biomarkers on patients with AMI, none of them have focused on SMuRF-less patients [29–31]. The logic behind this effort is that the metabolic and inflammatory status of patients have been shown to play a pivotal role in cardiovascular disease and specifically in CAD and ACS [32–40]. On top of that, genetic analyses, Mendelian randomization studies, and the determination of specific polymorphism responsible for atherogenesis in SMuRF-less patients should drive future research to elucidate additional pathogenetic aspects, and develop -potentially with the use of artificial intelligence- clinically relevant polygenic risk scores [41, 42].

Regarding imaging biomarkers, the innovation of the study lies in the fact that it recruits conventional and novel echocardiographic parameters and analytical angiographic assessment to unravel differences among SMuRF-less patients compared to patients with SMuRFs. As novel imaging modalities have proved, plaque vulnerability and rupture electromechanical complications are not always directly associated with systematically assessed biomarkers and risk factors such as dyslipidaemia [43, 44]. Moreover, an observational study by Figtree et al. indicated differences in the prevalence of left main and left anterior descending culprit lesions in SMuRF-less patients compared to those with SMuRFs [27]. As explained by the authors, this may be partly attributed to the family history of premature CAD and is an important finding potentially leading to a more adverse AMI risk profile in SMuRF-less patients. A potential criticism that our study could deal with is that differences in imaging parameters between patients with and without SMuRFs are likely to be the consequence of AMI rather than a predictive parameter. However, the main objective of the study is to identify associations of clinical, laboratory and imaging variables with SMuRF-less status which should be tested in future larger trials for their predictive value. Thus, the elaboration of additional biomarkers, such as imaging parameters, could contribute to the characterization of the clinical profile of SMuRF-less patients hospitalized with AMI, and shed light on the etiology of this emerging clinical entity. Finally, this study aims to provide data on the prognosis of SMuRF-less AMIs and evaluate emerging evidence highlighting the worse clinical course of these patients [3, 5, 6, 45–49]. The reason behind this observation could be correlated with increased time-to-reperfusion time due to reduced suspicion of AMI in these individuals, but also with undiscovered pathogenetic mechanisms and ‘‘hidden’’ comorbidities which might increase their cardiovascular risk.

### Limitations

Certain limitations of this study should be properly acknowledged. The main limitation is its observational nature which does not allow to conclude causal associations. Second, this study is not a multi-center one and its population consists of Greek patients exclusively. Future studies should be conducted to include and study other ethnicities and races to account for inherent variability of different patient populations and test the generalizability of our results. Moreover, the authors set an upper age limit as inclusion criterion in the study in an attempt to exclude very old patients with age-relating comorbidities and intricated AMI pathophysiology. As there are no evidence on cutoff values to support this limit, this could lead to selection bias in the study and ambiguous resuls across different age groups. Finally, our study -due to restricted resources- will study only some of the potential predictive laboratory biomarkers. Comprehensive and complete analysis of SMuRF-less patients’ metabolomic and genetic profiling should be taken into consideration for future research.

This real-world, prospective, non-interventional cohort trial study of patients hospitalized with AMI has the potential to identify clinical, laboratory and imaging biomarkers associated with the occurrence of AMI in SMuRF-less patients. SMuRF-less individual profiling could ultimately lead to the development of personalized risk-stratification models predicting adverse cardiovascular events.

